#### 6.5 Additional Details

---

**Participant Freedom:** The participant is free to attend with a companion. For all visits, individualized support by a research team member (preferably the same person) will be provided upon arrival. A taxi will be provided for all participant transportation.

**Imaging Appointments:** Depending on the availability of imaging slots, but always trying to accommodate the participants as much as possible (availability, fatigue, etc.) and ensuring adherence to protocol timelines, the PET and MRI scans may be separated into two visits.

#### 6.6 Detailed Procedures

---

##### Blood Sampling for Metabolism

---

##### **Blood test - metabolism**

- General panel\*: Complete blood count, renal function (creatinine), liver function (AST, albumin), thyroid function (TSH), inflammation marker (C-reactive protein).
- Metabolic profile (glucose, insulin, hemoglobin A1c, triglycerides, cholesterol, lactate, insulin, ketones\*\*).
- Metabolomics.
- Cytokines.
- Inflammatory profiles.

\*Upon admission to the PEP clinic, a general panel is performed (CBC, TSH, basic liver panel, basic renal panel, sodium, potassium, lipid profile, HbA1c). If the results are already available in the medical record, the panel will not be repeated during the "BEFORE" visit.

\*\*Certain analyses will be conducted in [name] laboratory. Plasma will be frozen for some analyses to be performed at a later time.

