#### Procedure:

- Fasting Blood Draw: 12 hours fasting required.
- Meal/snack provided after blood draw.
- Measurements: Weight, height, waist circumference.
- Blood pressure and pulse.
- Questionnaires will be done as listed in Table 1.
- Breaks will be offered to the participant (snack, coffee).

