### **8.1 Analyses**

All data will be compiled, and differences BEFORE vs. AFTER for the various measurement variables will be assessed using Wilcoxon signed-rank non-parametric tests for paired data.

Correlations will also be performed, particularly between brain function (variables related to global and regional changes in cerebral energy metabolism), blood levels of various measured parameters, and scores from clinical questionnaires (global psychopathology, functioning, depression, cognition, etc.).

In a second phase, comparisons will be made with a control group from a brain imaging database conducted in age-matched participants without the condition (Project 08-111 [name]).

The significance threshold will be set at  $p < 0.05$ . All statistical analyses will be performed using SPSS 24.0 software (SPSS Inc, Chicago, USA).

As this clinical study includes an exploratory component, new analyses or complementary analyses may be added based on the literature or preliminary analyses.

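### The clinic admission panel may replace the BEFORE blood panel with no stated fasting condition, and its contents do not match the study panel, so some exploratory pairs and HbA1c can be biased or lost

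*Protocol*

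**What the plan says.** Protocol section 6.4 sets one sampling condition for both clinical visits: "Fasting Blood Draw: 12 hours fasting required". Table 1 in section 6.3 schedules the blood test at PRE and at POST.

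Section 6.6 (Blood test - metabolism) lists what is measured. The first item, the general panel, carries an asterisk. It covers blood count, creatinine, AST and albumin, and ends with "thyroid function (TSH), inflammation marker (C-reactive protein". The second item has no asterisk on its heading: "Metabolic profile (glucose, insulin, hemoglobin A1c, triglycerides, cholesterol, lactate, insulin, ketones". The double asterisk on ketones only concerns where assays are run and the freezing of plasma.

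The single-asterisk footnote says that on admission to the clinic "a general panel is performed (CBC, TSH, basic liver panel, basic renal panel, sodium, potassium, lipid profile, HbA1c" and then that "If the results are already available in the medical record, the panel will not be repeated" at the BEFORE visit. It sets no fasting condition for the admission sample and allows no such substitution at AFTER.

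Section 8.1 states that "differences BEFORE vs. AFTER for the various measurement variables will be assessed using Wilcoxon signed-rank non-parametric tests for paired data". Section 8.2 lists HbA1c as a secondary variable. It lists triglycerides, cholesterol, blood count, creatinine, AST, albumin, TSH and CRP as exploratory.

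**The concern.** Section 6.4 aims to make the two members of each pair comparable by fixing the fasting state. The footnote can undo this for one member of the pair. The footnote describes the admission panel as routine, so substitution could be frequent.

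Two things are at stake. First, if a BEFORE triglyceride was taken after food and the AFTER value was fasting, the paired difference contains a sampling effect as well as any treatment effect. The signed-rank test remains valid as a test of the observed differences, but what those differences mean has changed. If non-fasting values run higher, a true rise is masked; with no true change, a spurious fall can appear. Second, an analyte that is in the study panel but not in the admission panel may never be measured at BEFORE. A baseline that was not drawn before treatment cannot be recovered in the analysis.

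The exploratory objective in section 4 names lipids and inflammation markers, and these are the measures the footnote can reach.

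**Working it through.** **Step 1. Compare the two panels (section 6.6).**

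| Analyte | Study general panel (asterisked) | Study metabolic profile (no asterisk) | Admission panel |
|---|---|---|---|
| Blood count, TSH | yes | no | yes |
| Renal and liver tests | creatinine, AST, albumin | no | basic renal and liver panels |
| CRP | yes | no | not listed |
| Triglycerides, cholesterol | no | yes | lipid profile |
| HbA1c | no | yes | yes |
| Glucose, insulin, lactate, ketones | no | yes | not listed |

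**Step 2. Apply the waiver under each reading.**

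- *Reading A: the waived panel is the asterisked study general panel.* CRP is skipped at BEFORE although admission did not measure it. Lipids and HbA1c stay in the metabolic profile on the fasting V1 draw.
- *Reading B: the waived panel is the admission panel as listed.* BEFORE lipids and HbA1c come from the admission sample, whose fasting state is not stated. CRP is not in that panel, so it is not waived.
- *Both readings:* blood count, creatinine, liver tests and TSH can come from admission at BEFORE and from V3 at AFTER.
- *Neither reading:* glucose, insulin, HOMA-IR, ketones, metabolomics and cytokines are not on the admission list. The PET variables use plasma sampled during PET (section 6.6, Blood Sampling During PET).

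**Step 3. Size under Reading A (CRP).** Section 5.1 plans 18 participants to reach 10 completers. Section 8.1 sets the threshold at 0.05; two-sided testing is assumed. With n untied, non-zero pairs, the smallest exact two-sided signed-rank p is 2/2^n:

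- n = 10: 2/1024 = 0.002
- n = 6: 2/64 = 0.031
- n = 5: 2/32 = 0.0625

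If 5 of 10 completers lack a BEFORE CRP, p < 0.05 is unattainable whatever the data show. At least 6 pairs are needed. The figure of 5 missing is an assumption; the protocol gives no rate.

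**Step 4. Size under Reading B (triglycerides), illustration only.** The protocol gives no figures to reproduce. Assumed: 10 pairs, log-SD 0.25 per measurement with independent errors, a true rise of 30%, and non-fasting values 10% to 30% higher. The rejection region is T ≤ 8.

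Apparent rise (geometric mean) = 1.30 / (1 + inflation)^(share substituted) − 1:

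- none substituted: 30%
- half: 1.30/1.10^0.5 = 1.24 and 1.30/1.30^0.5 = 1.14, so 24% down to 14%
- all: 1.30/1.10 = 1.18 and 1.30/1.30 = 1.00, so 18% down to 0%

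Simulated two-sided power is about 0.53 with none substituted, about 0.15 to 0.38 with half, and 0.05 to 0.26 with all. The lowest value is the null rejection rate: 50 of the 1024 sign patterns give T ≤ 8, and 50/1024 = 0.049.

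**Step 5. The opposite error.** Assume no true change and a sampling shift of 0.5 to 1.0 SD of the paired difference. The simulated false-positive rate is about 0.04 with none substituted, 0.10 to 0.20 with 5 of 10, and 0.29 to 0.78 with all 10. This applies only to analytes that respond to the sampling condition.

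**The case against.** The best defence is the layout of section 6.6. The asterisk is on the general panel alone, so the natural reading leaves triglycerides, cholesterol and HbA1c on the fasting V1 draw, and no fasting mix arises for them. The CRP loss can be answered in turn: the waiver depends on results being in the record, and a CRP that was never measured is not there. What both readings leave is small: exploratory safety-type analytes with no claimed fasting effect, taken a short time apart. Table 1 puts PRE at weeks 0-1 since admission, and section 6.4 puts the BEFORE visits within 10 days of the first psychiatrist visit.

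Much of this stands. A reader might infer that the footnote both removes CRP and contaminates the lipids. The text does not support both at once, because each harm rests most naturally on a different reading of the same sentence. A reader might also infer that admission samples are non-fasting; the protocol only leaves their state unstated. Nor is the study's main metabolic evidence compromised, since the PET variables, glucose, insulin, HOMA-IR and ketones are outside the footnote's reach.

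The defence does not remove the defect. The footnote hangs on one panel and describes another, each reading permits one of the two harms, and staff could apply it differently from one participant to the next.

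**Conclusion.** The point holds as a minor one. The footnote allows a BEFORE sample with no stated fasting condition to be paired with a fasting AFTER sample, and the mismatch between the two panels leaves open which analytes this touches. Under one reading CRP can lack a BEFORE value; under the other, BEFORE lipids and HbA1c can come from a non-fasting sample. Under both, blood count, creatinine, liver and TSH pairs can mix sampling occasions.

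The fasting issue is in practice about triglycerides, an exploratory variable. HbA1c is the only secondary variable touched and depends little on fasting. The p-value floor for CRP is exact arithmetic, conditional on how many pairs are lost. The power and false-positive figures for a fasting mix rest wholly on assumed inputs: they show what could happen, not what this protocol will produce.

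**What to change.** For every variable analysed BEFORE against AFTER, delete the substitution. State that lipids, HbA1c, CRP and the rest of the general panel are run on the fasting V1 sample, and keep admission results for eligibility and safety only. This settles both readings. If an admission triglyceride has to be used, flag it and leave that pair out of the paired test.

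The cost is one routine laboratory panel for up to 18 participants, with no extra visit or needle, because V1 already includes a fasting draw. The change should be made before enrolment, since a missing pre-treatment sample cannot be obtained later.

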### MRI Imaging

---

No specific preparation is required by the participant. Upon arrival, the participant must wear a hospital gown and remove any metallic objects (jewelry, watches, glasses, hearing aids, dental prostheses). It is crucial to remove all metallic objects (buttons, staples, hair clips, zippers).

#### Procedure:

- The participant will lie on their back on a bed that moves into the MRI machine (MRI3T Ingenia Philips).
- The imaging session will take about 10 minutes (plus installation time), during which the participant must avoid moving their head.
- The MRI machine and head coil used in this study are approved by Health Canada and are routinely used at the CHUS Research Center.
- The participant will be monitored throughout the imaging session, and verbal communication will be possible at all times during the exam.

### PET Scan Procedure

---

Two intravenous catheters will be placed in the forearms, and blood glucose will be measured.

- Approximately 15 minutes before the radiotracer injection, the participant will be encouraged to lie down on the examination gurney or on a gurney in a room adjacent to the examination room.
- CT scan will be performed for a few minutes before the PET scan acquisition begins.
- The radiotracer, adjusted to a volume of 5 to 10 ml of saline (NaCl 0.9%), will be injected through one of the catheters.
  - 11C-Acetoacetate:370 MBq (10 mCi)
  - 18F-FDG:185 MBq (5 mCi)
- The PET scan will last 20 to 30 minutes (depending on the radiotracer).
- Repeated blood samples will be taken during the various PET scan acquisitions (10 ml per PET scan) through one of the catheters.
- Since two radiotracers are used during a single imaging session, there will be a 15 to 30-minute break; the participant will be invited to get up, walk around, and use the restroom.
- After the imaging session, the participant's overall health will be checked, and a snack will be provided.

### Blood Sampling During PET

---

For each PET exam, plasma fractions will be separated by centrifugation, and plasma radioactivity will be immediately counted using a scintillation counter to evaluate the radiotracer's blood kinetics. Plasma will then be used to measure glucose and ketones (for tracer uptake calculations).

### Continuous Glucose Monitoring

---

Glucose levels will be monitored using a continuous glucose monitor (Dexcom G7). This portable device features a small disposable sensor that tests glucose levels every five minutes and sends this information

to a transmitter throughout the day and night. The readings are relayed in real-time to a device that can be read by the patient, caregiver, or healthcare provider, even remotely.

The sensor is worn under the skin (often on the abdomen or arm). The sensor will be placed by the nurse during the metabolic visit, and glucose values will be recorded for about 10 days (8 to 12). The participant will wear a sensor at two points during the project: at the beginning and the end of the study.

## 6.7 Participant Collaboration

---

The participant must pay attention to certain instructions while wearing the glucose monitor, such as limiting continuous immersion in water (e.g., bathing, swimming) and charging their smartphone every night.

## 6.8 Radiotracers Used

---

The radiotracers are produced and distributed by the Centre for Molecular Imaging of Sherbrooke (CIMS). CIMS has cyclotrons for the production of radiotracers for clinical and research use. This production is done according to good manufacturing practices (GMP). The standard operating procedures for synthesis and quality controls are done in collaboration between the principal investigators, a radiochemist, and a pharmacist. The standard operating procedures or the investigator's brochure can be consulted upon request. In addition, a regulatory affairs officer and a quality control officer are in place to ensure compliance with GMP and monitoring during the study.

**18F-FDG:(Gludef® Lantheus Imaging)** - Sterile solution, intravenous administration, Health Canada approved for clinical use.

**11C-Acetoacetate**: Sterile solution, intravenous administration, CHUS has Health Canada approval for research use.

## 6.9 Participant Withdrawal

---

When the participant stops or is withdrawn from the study, no further data collection or final visit will occur except to document any adverse events that have occurred since the last visit or follow up with the participant to remove the continuous glucose monitor. All data and samples collected until the participant's withdrawal will be retained per applicable standards.

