#### Psychotic Disorders and Metabolic Impacts

---

People with psychotic disorders are twice as likely to die from cardiovascular accidents and have a fourfold higher risk of obesity. APs have significant metabolic side effects, such as weight gain and altered glucose and lipid homeostasis. This increases the risk of developing obesity, type 2 diabetes, and cardiovascular diseases. Moreover, some researchers have shown a positive association between symptom improvement after taking APs and metabolic disturbances, although this link remains controversial. Nonetheless, this suggests common mechanisms between the action of APs and their side effects.

It is generally accepted that interventions aimed at combating these metabolic side effects (notably by prescribing oral antidiabetics to improve insulin sensitivity) do not worsen psychiatric symptoms.

Regarding nutritional interventions, although this is a promising field, few interventions focus on the evaluation and management of the nutritional and metabolic aspects of these patients. Furthermore, weight gain induced by APs is one of the most burdensome side effects and often leads to discontinuation of treatment.

It is important to note that patients experiencing a first episode of psychosis already exhibit certain glucose homeostasis disturbances, such as insulin resistance or prediabetes, even before starting APs. This metabolic disruption could, therefore, be intrinsic to psychotic disorders, independent of the metabolic effect of APs. A meta-analysis comparing AP-naïve patients with glucose dysregulation without psychiatric illness concluded that both groups exhibit a similar gene expression signature. A second meta-analysis focusing on obesity markers also demonstrated a difference between healthy controls and AP-naïve psychotic patients experiencing a first episode of psychosis. Several aspects of brain energy metabolism may be disrupted in psychotic disorders, such as insulin and glucose signaling, glycolysis, astrocyte-neuron coupling, and ATP production by brain cells.

Studies have also linked negative and cognitive symptoms to glucose metabolism dysfunction in the prefrontal cortex, particularly in patients with schizophrenia and who are AP-naïve.

However, according to our review of the literature, there is no data regarding ketone metabolism, the brain's main alternative fuel to glucose, in patients with psychosis.

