### 5.1 Sample Size

---

This is a pilot observational study. Currently, there are no studies that have measured cerebral use of 11C-Acetoacetate before and after AP administration. We must rely on our previous studies on energy metabolism, which showed differences in the same variables with groups of 7 to 15 participants.

Number of participants: 18 participants to reach 10 who complete the study. This pilot study will allow us to obtain preliminary data to secure funding for future studies.

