### 5.4 Withdrawal Criteria During the Study

---

The participant's participation in the research may be terminated by the responsible researchers or the participant themselves. This will occur if new discoveries or information indicate that participation in the study is no longer in the participant's best interest, if it becomes apparent that the participant is not following the study's guidelines, or if there are administrative reasons to abandon the study.

Definitive withdrawal from the study will occur in the following cases:

- Voluntary withdrawal. A participant may withdraw their consent to participate in the research at any time without affecting the services and treatments offered.
- Inability to complete initial visits within the 10-day timeframe.
- Initiation of AP medication (other than what is permitted under concomitant medication below) before completing the 2 "BEFORE" visits (depending on the participant's desire or clinical changes).
- Any changes deemed by the responsible physician to be contraindications to continuing in the study (significant renal or hepatic insufficiency, etc.).

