### 7.6 Significant Incidental Findings

---

Following the various tests and examinations in the project, it is possible that significant previously unknown anomalies may be identified that are important for the participant's health. In such a case, the participant will be informed, and one of the project's referring physicians will ensure appropriate medical follow-up. It is possible that they will contact the family doctor or other specialists to ensure the participant is properly taken care of. An incidental finding could exclude the participant from the project.

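### Section 6.9 ends all data collection at any exit from the study, even for a participant removed by the researchers who would still attend the clinical AFTER visit

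*Protocol*

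**What the plan says.** Section 6.9 sets one rule for every exit: "When the participant stops or is withdrawn from the study, no further data collection or final visit will occur except to document any adverse events". It adds that contact may also be made to take off the glucose monitor. What was gathered earlier is kept: "All data and samples collected until the participant's withdrawal will be retained per applicable standards".

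Some exits are decided by the researchers and not by the participant. Section 5.4 allows termination "if it becomes apparent that the participant is not following the study's guidelines, or if there are administrative reasons to abandon the study", and also for changes that the responsible physician regards as a contraindication, with kidney or liver impairment as examples. Section 7.5 says that the researchers may end participation without the participant's agreement. Section 7.6 adds: "An incidental finding could exclude the participant from the project".

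Section 5.1 plans for "18 participants to reach 10 who complete the study". Section 8.1 says that BEFORE/AFTER differences "will be assessed using Wilcoxon signed-rank non-parametric tests for paired data". Section 8.2 lists BPRS change and plasma glucose, insulin, HbA1c and HOMA-IR as secondary variables, and weight and lipids as exploratory ones. Their AFTER values come from V3, a two-hour clinical visit without imaging (section 6.4). V4, the second PET, takes place at another site.

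**The concern.** A person removed by the researchers after the BEFORE visits may be perfectly willing to return for a blood draw, a weight measurement and the questionnaires, yet section 6.9 rules that out. The missing AFTER values may not be missing at random. Among the grounds for removal are new medical findings, and the study is about metabolic disturbance under treatment. The background in section 3 also says that "weight gain induced by APs is one of the most burdensome side effects and often leads to discontinuation of treatment".

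At stake is how far the BEFORE/AFTER results on symptoms and systemic metabolism describe those who began treatment, as opposed to those who stayed to the end. With about 10 pairs, a few selectively missing ones can move the estimate. The limitations in section 7.11 cover diagnostic mix, drug type and dose, adherence, substance use, diet, the control group and glucose monitoring. They do not mention attrition.

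**Working it through.** **Inputs.** Enrolled 18 and completers 10 (section 5.1). Paired signed-rank tests (section 8.1). No follow-up after exit (section 6.9). The protocol gives no dropout rate, no timing of losses and no effect size.

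**1. The plan's own figure.** 18 − 10 = 8, and 8/18 = 44.4% implied non-completion. Inflating back gives 10/(1 − 8/18) = 18. This is circular: it shows that the two numbers agree, not that the rate is justified.

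**2. Which losses matter.** Two of the four definitive-withdrawal reasons in section 5.4 (missing the 10-day window, and starting an antipsychotic before both BEFORE visits are done) can only arise before the BEFORE set is complete. The change of mind described in section 7.1 also falls in the period before treatment. Such participants never have a BEFORE/AFTER pair to lose. Let k be the number of the 8 who leave after the BEFORE visits and before V3; k can be anything from 0 to 8.

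**3. Share without an AFTER value.** Of the 10 + k participants with complete BEFORE visits, the share without AFTER data is k/(10 + k).

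**4. Effect on the mean change.** If completers have mean change c and leavers would have had mean change l, the mean over all 10 + k is (10c + kl)/(10 + k). The completers-only mean differs from it by k/(10 + k) × D, where D = c − l. D is an assumption, shown at 0.5 and 1 SD.

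| k | 10 + k | share missing | shift, D = 0.5 SD | shift, D = 1 SD |
|---|---|---|---|---|
| 0 | 10 | 0% | 0 | 0 |
| 2 | 12 | 16.7% | 0.08 SD | 0.17 SD |
| 4 | 14 | 28.6% | 0.14 SD | 0.29 SD |
| 6 | 16 | 37.5% | 0.19 SD | 0.38 SD |
| 8 | 18 | 44.4% | 0.22 SD | 0.44 SD |

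**5. What offering V3 could recover.** Between 0 and 8 V1/V3 pairs, so 10 to 18 pairs in all. The upper end needs every loss to fall after the BEFORE visits and every leaver to consent and attend.

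**6. Which analyses gain.** V3 alone serves BPRS change, the plasma measures, weight and the questionnaires. It adds nothing to the primary objective (PET change) or to the part of secondary objective 1 that relates PET change to clinical and systemic change. Both of these need V4.

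**The case against.** The strongest reply is that this is a small observational pilot meant to give preliminary data, that stopping collection at study exit is a legitimate choice, and that those who withdraw consent could not be followed in any case. It is also true that many of the 8 losses may occur before treatment begins, when they cannot distort a paired contrast. All of this stands and limits the size of the point. It does not explain why a willing participant removed by the researchers should also lose a clinical visit that the schedule already contains.

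A reader might infer more than the documents support:

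- **That AFTER data come only from people who tolerate and take the drug.** Section 6.9 is triggered by leaving the study. Stopping the antipsychotic after the BEFORE visits is not a listed withdrawal reason. Section 5.2 accepts changes of type and dose, and section 5.5 accepts other medication. Side effects (UKU) and adherence (MARS) are measured at V3, and section 7.11 expects imperfect adherence among those studied.
- **That declining the second PET cancels V3.** Nothing says so. V3 is listed before V4, and a V3 already done is retained.
- **That nothing will be known about leavers.** Their BEFORE data are kept, and section 9.3 records dropouts. Only their AFTER data are missing.
- **That the protocol itself ties study exit to outcome.** The section 3 sentence concerns stopping treatment in general, not leaving this study of five to seven weeks. It makes informative loss plausible but does not establish it.
- **That a particular gain, such as 4 extra pairs or 40%, can be expected.** That would need a split of the 8 losses, which the protocol does not give.

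**Conclusion.** The point holds in a limited form. Section 6.9 is an explicit rule that treats removal of a willing participant like withdrawal of consent. As a result, AFTER values for the secondary clinical and systemic variables and for the exploratory ones are confined to those who remain in the study. Implied non-completion is 44%. The part that falls after the BEFORE visits is unknown, so the recoverable V1/V3 pairs range from 0 to 8. The shift in a completers-only mean ranges from 0 to 0.22 SD if completers and leavers differ by 0.5 SD, and up to 0.44 SD if they differ by 1 SD. These shifts rest on assumed values of k and D and show what is possible, not what is expected. The primary PET comparison benefits only where V4 is also done. The change is worth making because it is cheap and can only reduce the loss of data that may be informative.

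**What to change.** - **Section 6.9:** end all collection only when the participant withdraws consent to data collection. In every other exit after completed BEFORE visits, offer V3 at its scheduled time, and V4 if the participant is willing and medically able.
- **Section 5.4:** reconcile the ground of not following study guidelines with sections 5.2 and 7.11, which accept real-world antipsychotic use. The investigators should state whether stopping or irregular intake counts under that ground.
- **Section 9.3:** record the timing and reason of each exit alongside the dropout data already tracked.
- **Section 8.1:** compare leavers with completers on the retained BEFORE data and on any V3 data. With at most 8 leavers this would be descriptive.
- **Section 7.11:** list attrition as a limitation.

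The cost is protocol and consent wording plus a few V3 visits that are already in the schedule. Compensation is CAD 60 per V3 (section 7.3), so at most 8 × 60 = CAD 480, plus transport, staff time and laboratory work. No new procedure is needed. Some leavers will decline, and a V3-only visit leaves the primary PET sample unchanged.
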